### Lung and hearing examination

Respiratory Function Tests (RFT);Tonal audiogram.

**Blood sampling**: exploring metabolic and hormonal disorders.
Carbohydrate-lipid balance: fasting blood glucose and insulin, lipid fractions, triglycerides;Hepatic: transaminases (TGO, TGP), Aspartate Aminotransferase (ASAT), Alanine Aminotransferase (ALAT), Alkaline Phosphatase (PAL), Gamma-glutamyl transferase (GGT), Lactate dehydrogenase (LDH);Hormone balance: sex hormone binding globulin (SHBG), Luteinizing hormone (LH), Follicle-stimulating hormone (FSH), Estradiol, Anti-Müllerian hormone (AMH), thyroid stimulating hormone (TSH).Osteocalcic balance: calcium, phosphorus, vitamin D;Renal assessment: ionogram, creatinine;C-reactive protein (CRP) + highly sensitive CRP.

Compensation is offered to cover the costs of transport and to compensate one day off work.

The overview of study assessments and procedures can be found in Table 3.

**The costs of the sequelae** will be estimated for the 140 patients. Standard unit costs will be calculated for each type of sequelae using data from the financial departments of the participating hospitals, as well as the published literature [37]. The average costs will be assessed and compare between both patient groups. One-way sensitivity analyses will be conducted by varying parameters by plus or minus 20% and illustrated graphically in a Tornado diagram.

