### Statistical analysis

#### Sample size

**Step 1 = 268 participants**

The first aim is to show a difference in the proportion of patients with chronic fatigue (≥1 dimension of MFI-20) in the group of interest as compared with each of the control groups. The pairwise comparison will be performed using the χ^2^ test (one-tailed test under the assumption of higher chronic fatigue in the chemotherapy group of interest) at a risk α = 0.05 and a power level of 80% (1-β = 80%). Assuming that 25% of patients express chronic fatigue in the group of interest as described in testicular cancer [20] and 10% in each of the control group, the required sample size, with a 2:1 allocation ratio in favor of the group of interest, is 121 subjects in the group of interest and 61 subjects in each of the two control groups (patient control and healthy control).. To anticipate 10% of non-assessable women, we plan to enroll 134 survivors in the group of interest, 67 survivors in the control group, and 67 healthy controls.

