**Step 2 = 135 patients**

Assuming around 66% of patients will accept to participate, 90 patients in the group of interest and 45 patients in patient control group are expected to agree to participate.

Assuming 10% of non-assessable participants (around 80 and 40 survivors in the group of interest and control group, respectively), and a proportion of patients experiencing cardiac sequelae varying from 5 to 35% (with a 95% interval confidence) according to literature for testicular cancer [38], it will be possible to estimate the frequency of cardiac sequelae with a precision of 4.8 to 10.5%, in the group of interest and 6.8 to 14.8% in the control group.

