#### Planned analysis

Data analyses will be conducted according to the statistical methods used in paired case-control studies, as follows:
Descriptive analysis of patients’ and controls’ participation and according to sociodemographic and clinical data (including tumor type), quantitative QoL scores and data on living conditions in patients and controls, and then in patients based on medical data related to cancer.Statistical comparison using a univariate and multivariate analysis (ANOVA, or Kruskal-Wallis test, or Mc Nemar χ2 test depending on the nature of the variables and GLM (Generalized Linear Model) model with a Bonferroni correction):Socio-demographic features and comorbidities;Reintegration and sequelae data, then by subgroup (including fertility-sparing);

A prognostic model for predicting QoL or living conditions has been constructed using an adapted model (GLM), taking into account the time since end of treatment and controlling for effect of center.

Medical and biological parameters are the categorical variables. They will be compared between the two groups of patients and then between sub-groups according to time since end of treatment (short term and long-term follow-up) using the χ2 test or the Fisher exact test.

Costs will be compared using the Wilcoxon-Mann-Whitney test. Standard multivariate analyses will be implemented in order to control the potential selection bias. Uncertainties regarding costs of the sequelae will be assessed by probabilistic analysis using nonparametric bootstrap methods: 1000 simulated bootstrap samples will be generated by independent draws. All 95% confidence intervals will be computed. All analyses will be performed using STATA software version 16.0 (StataCorp, College Station, TX).

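### The plan sets out to compare average sequelae costs but names a rank test, which does not test a difference in means; separately, the count of 140 costed patients should be reconciled with Step 2.

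*Protocol article*

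**What the plan says.** Costs of sequelae are a secondary objective of Step 2 (Secondary objectives). The cost paragraph under Lung and hearing examination says that standard unit costs will be calculated for each type of sequela, that costs "will be estimated for the 140 patients", and: "The average costs will be assessed and compare between both patient groups".

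Planned analysis then gives the method: "Costs will be compared using the Wilcoxon-Mann-Whitney test". It adds multivariate analyses of unspecified form to control selection bias, and a nonparametric bootstrap with 1000 samples for uncertainty in the costs. It also says that 95% confidence intervals will be computed. It does not say which parameter the bootstrap targets.

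On numbers, the sample size section is headed "Step 2 = 135 patients" and states that "90 patients in the group of interest and 45 patients in patient control group are expected to agree to participate".

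**The concern.** The quantity and the test do not match. A comparison of average costs is a comparison of arithmetic means. The Wilcoxon-Mann-Whitney test asks whether a randomly chosen patient in one group tends to cost more than a randomly chosen patient in the other. The two questions coincide when the distributions have the same shape and differ only by a shift, and the article does not say so.

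Unit costs are attached to sequelae, so a woman with no costed sequela would presumably contribute zero, and women with several or serious sequelae would contribute much more. If so, the distributions may differ in shape as well as location. The report could then show clearly different mean costs with a non-significant p-value, or similar means with a significant one, and nothing in the article says which result prevails. The Discussion looks ahead to effects on public health expenditure. Total expenditure follows from mean cost times number of patients, so the mean is the relevant quantity.

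The figure of 140 patients is a separate matter. It is phrased as a definite group, but no such group appears elsewhere in the design.

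**Working it through.** **1. Target and test side by side.** The cost paragraph (Lung and hearing examination) sets average cost per patient group, compared between groups. Planned analysis names a rank test and no other test for that comparison. The bootstrap is tied to uncertainty, and the difference in means is not named as its target.

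**2. Can the rank test and the means disagree at these sample sizes?** The documents give no cost distribution, so every cost input below is assumed. The group sizes are the plan's: 90 versus 45 enrolled, about 80 versus 40 assessable. Tests are two-sided at 5%.

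*Continuous costs, different spread.* Lognormal costs, log-SD 1.5 versus 0.8.
- Equal means of 1,000: the median is 1,000 × exp(−σ²/2), so 1,000 × exp(−1.125) = 325 versus 1,000 × exp(−0.32) = 726. The rank test rejects in about 95% of runs at 90 versus 45 (93% at 80 versus 40), although the mean difference is zero.
- Equal medians of 500: the mean ratio is exp((1.5² − 0.8²)/2) = exp(0.805) = 2.24. The rank test rejects in about 3.4% of runs (3.7% at 80 versus 40), although the means differ more than twofold.

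*Costs with many zeros, constructed to pull in opposite directions.* Chemotherapy: 15% of women at 10,000, mean 0.15 × 10,000 = 1,500. Surgery alone: 30% at 2,000, mean 0.30 × 2,000 = 600. The mean ratio is 2.5. P(chemotherapy > control) = 0.15, and P(control > chemotherapy) = 0.30 × 0.85 = 0.255. At 90 versus 45 the rank test declares surgery alone costlier in about 28% of runs and almost never declares chemotherapy costlier. A bootstrap interval for the mean difference lies above zero in roughly two thirds of runs and never below.

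*Costs with many zeros, in the direction of the study hypothesis.* 30% versus 12% affected, 5,000 each: means 1,500 and 600, again a ratio of 2.5. At 90 versus 45 the rank test detects the difference in about 65% of runs and the bootstrap interval in about 70%. Neither points the wrong way.

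Disagreement is therefore possible, and its extent depends on inputs that the article does not give.

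**3. The count of 140.** Inputs are from the sample size section.
- Step 2 enrolled: 90 + 45 = 135, which reproduces the plan's total.
- Step 2 assessable, using "Assuming 10% of non-assessable participants (around 80 and 40 survivors in the group of interest and control group, respectively": 80 + 40 = 120 (135 × 0.9 = 121.5 before rounding).
- Step 1 survivors: 134 + 67 = 201. The stated acceptance of around 66% gives 0.66 × 201 = 132.7, and two thirds gives 134.
- 140 would need 140/201 = 69.7% acceptance.

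None of these gives 140. The excess over 135 is 5 patients, 5/135 = 3.7%. The Step 2 precision figures rest on 80 and 40: 1.96 × √(0.05 × 0.95/80) = 4.8% and 1.96 × √(0.35 × 0.65/80) = 10.5%, and with n = 40, 6.8% and 14.8%. All four match the plan, so 140 enters no calculation.

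**The case against.** The strongest reply is that much of the remedy is already in the plan. Average costs will be reported, a 1000-sample bootstrap is specified, and confidence intervals are promised. On a natural reading these yield mean costs with bootstrap intervals, and the rank test is one element beside them. An article may leave the order of priority to the full protocol. This stands as mitigation. It does not remove the point, because the article is not silent: it names a test for the comparison, and that test does not address the stated quantity.

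A reader might infer more, namely that the rank test will miss or reverse the true cost difference. The documents do not support that. They give no cost distribution, and standard unit costs with many types of sequela examined may limit both extremes and zeros. The reversal example gives surgery-alone women twice the sequela frequency of chemotherapy women, against the study's own hypothesis. It also needs a fivefold gap in cost per affected woman, although unit costs attach to the sequela and not to the group. With frequencies in the hypothesised direction and equal unit cost, the two methods nearly agree.

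A reader might also infer that 140 is a wrong denominator that distorts the averages. That is not supported either: averages will be taken over whoever has data. Nor is the intended figure beyond doubt. Costs are a Step 2 objective, but Table 2 lists EQ-5D under the cost assessment, and Table 3 collects EQ-5D in Step 1, where survivors number 201.

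**Conclusion.** The mismatch is real and limited. The plan states a comparison of means and names a test that does not test means unless the distributions differ only by a shift. How far the two answers diverge cannot be determined from the documents. Under assumed inputs it ranges from near agreement (about 65% versus 70% detection) to rejection in about 95% of runs with equal means. The planned bootstrap mitigates this in part, but without a named target or priority it does not settle which result is the comparison. Costs are secondary, and no primary conclusion or sample size depends on them. It is worth correcting because the correction is almost free.

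The 140 is a minor inconsistency to reconcile with 135 enrolled and about 120 assessable, with no effect on any calculation shown.

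**What to change.** In Planned analysis, define the cost comparison as the difference in arithmetic mean cost between the two patient groups, with a 95% confidence interval from the 1000-sample nonparametric bootstrap already planned. State whether the resampling respects the age matching of patient controls in Table 1. Keep the Wilcoxon-Mann-Whitney test as descriptive only. Run the planned multivariable adjustment with a model for mean cost that allows zeros, for example a two-part model; a plain gamma model would not accommodate zero costs.

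In the cost paragraph, reconcile the 140 patients with Step 2 as sized (90 + 45 = 135, about 120 assessable), or say which other population is meant.

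This is a change of wording, with no new data, visits or patients. The downside is that with skewed costs the interval for the mean difference may be wide at about 80 versus 40 assessable patients.

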## Discussion

Regarding the late effects of chemotherapy in testicular cancer survivors, some of which occur as early as in the first year after treatment, and the lack of data in ovarian GCT and SCST survivors, research is needed on these issues in rare ovarian cancer survivors, particularly germ cell and sex cord stromal tumors, i.e. the main non-epithelial ovarian cancers.

To our knowledge, this is the first large multicenter case-control study to assess chronic fatigue, several domains of QoL and to explore the late effects of chemotherapy, particularly cardiovascular and pulmonary disorders and neurotoxicity. The study is based on the INCa French Network TMRG – GINECO and is representative of the French population treated for ovarian GCT and SCST. It offers the opportunity to better understand the impact of cancer and chemotherapy on long-term fatigue and quality of life in a large population of non-epithelial ovarian cancer survivors. The comparison with (i) patients treated with surgery alone and (ii) women without cancer will provide information about the needs and concerns of these patients at distance from treatment, i.e. follow-up of fertility, parental projects, social and professional integration, etc. The expected results will further understanding of the post-treatment period in survivors of rare cancer, especially young women.

The rigorous medical work-up conducted nationwide and focusing on the late effects of chemotherapy, with a focus on cardiovascular and pulmonary disorders, will provide important data about the physical and functional late effects of chemotherapy. As a result, intervention strategies could be proposed to improve the management of these patients during treatment and in the long term. In addition, specific strategies for post-treatment care and follow-up will become possible. These longitudinal evaluations will allow the late effects of cancer treatments to be measured and conclusions to be drawn.

In terms of public health, the detailed information that will be provided by this ambitious multidisciplinary research, involving oncologists, cardiologists, vascular physicians, otorhinolaryngologists and pneumologists, is the prerequisite for envisaging interventional strategies and treatments for these patients over time. The identification of sequelae would fuel recommendations regarding practices and chemotherapy regimens that reduce toxicity while maintaining efficacy. In the long term, the resulting preventive actions against the potential side-effects of chemotherapy identified in this research would have a beneficial impact on public health expenditure.

This original study will provide important data on the potential long-term physical side-effects of chemotherapy, especially cardiovascular and pulmonary disorders, neurotoxicity and the impact on quality of life. Based on the expected results, intervention strategies could be proposed to improve the management of these patients during their treatment and over time. By identifying the long-term side-effects of these chemotherapy regimens, it will be possible to produce recommendations aiming to reduce their toxicity while maintaining their efficacy.

### Trial status

Recruiting.

## Data Availability

The datasets used and/or analyzed during the current study are available from the corresponding author on reasonable request. Grant number: ARC 2016 PGA1 20160203900.

## Abbreviations

AMH: Anti-Müllerian hormone
BEP: Bleomycin, Etoposide and Cisplatin
CT: Chemotherapy
eCRF: electronic case report form
FSH: Follicle-stimulating hormone
GINECO: Groupe d’Investigateurs Nationaux pour l’Étude des Cancers Ovariens et du sein
GCT: Germ Cell Tumor
INCa: Institut National du Cancer
QoL: Quality of Life
SCST: Sex Cord Stromal Tumor
SHBG: Sex Hormone Binding Globulin
SPIRIT: Standard Protocol Items, namely Recommendations for Interventional Trials
TMRG: Tumeurs Malignes Rares Gynécologiques
t-PA: *tissular* Plasminogen Activator
TSH: Thyroid Stimulating Hormone
VWf: Von Willebrand factor
